
## **10. Analysis Plan**

Our primary outcome is time to readmission for any cause. The primary comparison will be the times to events compared between the intervention arm and the usual care arm; that is, the primary hypothesis is whether a series of interventions, adapted to the behavior and outcomes of each particular patient, will reduce readmission rates compared to usual care. We expect the 1-year event rate to be 47% in the

## Remote monitoring and behavioral economics in managing patients discharged from the hospital with heart failure: a randomized clinical trial

usual care arm based on data obtained on our target population at UPHS. We wish to have 80% power to detect an absolute decrease in this rate of about 10% in the intervention group; this corresponds to a hazard ratio of 0.73. We will accrue 566 patients over the 24-month enrollment period and follow them for an additional 12 months; with the 1:1 randomization ratio, we will have approximately 283 subjects in each arm. The primary hypothesis test will use a two-sided Type I error rate of 0.05. Note that the power calculations are based on the time to first readmission; if patients experience multiple readmissions, statistical power will be increased. Prior to analysis, we will produce data summaries including graphical methods to assess data quality, examine central tendencies and distributional assumptions and randomization success. The primary analysis will consist of an unadjusted intent-to-treat hypothesis tests using the Andersen-Gill formulation of the Cox proportional hazards model to compare the times to hospitalizations in the two groups; these models properly adjust for the correlation of multiple repeated events within individuals. We will also estimate multivariate regression models adjusted for the stratification variable and other covariates of interest (such as patient sex, income, race, baseline ejection fraction, and quality of life), retaining these given evidence of confounding or predictive ability. We will employ a confounder selection method based on "change in estimate" criterion. We will assess interaction terms between the a priori potential effect modifiers such as income level, race, and baseline ejection fraction. All hypothesis tests will be two-sided and models will be assessed using standard diagnostic techniques. We will use standard approaches to assess the modeling assumptions and include interaction terms with time if necessary. Handling of missing data is an important issue in all RCTs. Follow-up data may be missing if participants miss the follow-up visit or withdraw. Even in subjects who are lost to follow-up, we will be able to capture any events that result in hospitalization, and thus will still be able to observe our primary outcome. This includes hospital discharges from Penn Medicine as well as obtaining state-based discharge data and from Pennsylvania, New Jersey and Delaware to ensure that all readmissions that occur outside of Penn Medicine are captured. In addition, some subjects may receive a heart transplant during the course of the study. Because the disease trajectory and treatment paradigm change significantly with that event, we will censor patients at the time of transplant; the admission to conduct the transplant will count as an event, but follow-up will cease then and patients will be removed from the risk set. We will compare dropout rates by arm, will attempt to find the reasons for missing data and will compare baseline characteristics in participants with complete vs. incomplete follow-up. If enrolled intervention patients receive a heart transplant or ventricular assist device during their 12 month participation they will no longer be eligible to participate in the remote monitoring and their data will be censored from the date they receive the transplant or VAD going forward. An additional secondary endpoint will be cause-specific rehospitalizations, the rationale being that evaluating cause-specific hospital admission will allow a more complete understanding of the potential effects of the intervention, by indicating how many of the readmissions are due to what cause (e.g., heart failure, MI, stroke, other cardiovascular cause, noncardiovascular cause, etc). In secondary analyses we will investigate the sensitivity to modeling assumptions using imputation models and inverse-probability-weighted estimating equations and models that adjust for informative missing data. Patient days spent hospitalized, in rehab or at a SNF will not count towards adherence and will be removed from numerator and denominator and considered unmeasurable for adherence. For the qualitative interviews, the Research Scientist and Clinical Research Coordinators will review all data for recurring themes. As our interest is in the differences and similarities between the groups of patients noted above, we will conduct cross-case analyses to identify the factors that may be associated with patient adherence and readmission. The analysis will consist of describing factors in each of the groups and then comparing those factors across groups.

To assess the cost-effectiveness of the interventions, we will use analytic methods for economic evaluations in clinical trials. Our approach will be similar to Specific Aim 3 using cost as the outcome. We

Remote monitoring and behavioral economics in managing patients discharged from the hospital with heart failure: a randomized clinical trial

will use generalized linear models to adjust for the stratification variable and other factors. Cost-effectiveness ratios will be calculated as the difference in costs divided by the difference in rehospitalization rate calculated under Specific Aim 3 for the “within-trial” analysis, with parametric 95% CIs for the cost per percentage point increase in adherence and acceptability curves. Standard errors and the correlation of the difference in cost and effect will be obtained using a bootstrap procedure. A further cost-effectiveness analysis from the “societal perspective” will be conducted to assess the impact of the rehospitalization rate reductions measured as cost per QALY gained. To address uncertainty in the micro simulation model, we will also conduct a probabilistic sensitivity analysis (PSA162) by defining probability distributions for the variables in the model used to calculate costs and effectiveness. We will use the results of the PSA to calculate confidence (or credible) intervals and acceptability curves

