#### *7.6. Key Exclusion Criteria*

Patients will be excluded from study participation if they are less than 18 years old or older than 80 years old, will not or cannot provide informed consent, have a markedly shortened life expectancy (either listed, have history of or are being evaluated for heart transplant, listed for or being evaluated for a ventricular assist device, are inotrope dependent, have metastatic cancer, are currently receiving palliative care/hospice), have end-stage renal disease, if their glomerular filtration rate is less than 25 ml/min, if they are on dialysis, or are medically unstable, or if their heart failure is managed with a CardioMEMS monitor. Patients will also be excluded from study participation if they are receiving another remote monitoring/telemedicine intervention or if they are receiving follow-up care outside of UPHS. They are also ineligible if they participated in the CHF pilot study. Patients will be excluded if they have a current cognitive or psychiatric condition to be defined as: psychosis schizophrenia/schizophreniform disorder, schizoaffective disorder; severe cognitive impairment (traumatic brain injury); suicidal ideation/attempt; mania (separate from psychosis, but still affecting ability to consent/participate); substance abuse; dementia.

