### Data analysis plans

Prior to analysis, we will produce data summaries including graphical methods to assess data quality, examine central tendencies and distributional assumptions and randomization success. The primary analysis will consist of an unadjusted intent-to-treat hypothesis test using the Andersen-Gill formulation of the Cox proportional hazards model to compare the times to hospitalizations in the two groups; these models properly adjust for the correlation of multiple repeated events within individuals.. We will also estimate multivariate regression models adjusted for the stratification variable and other covariates of interest (such as patient sex, income, race, baseline ejection fraction, and quality of life), retaining these given evidence of confounding or predictive ability. We will employ a confounder selection method based on "change in estimate" criterion. We will assess interaction terms between the a priori potential effect modifiers such as income level, race, and baseline ejection fraction. All hypothesis tests will be two-sided and models will be assessed using standard diagnostic techniques. We will use standard approaches to assess the modeling assumptions and include interaction terms with time if necessary.

Handling of missing data is an important issue in all RCTs. Follow-up data may be missing if participants miss the follow-up visit or withdraw. Even in subjects who are lost to follow-up, however, we will be able to capture any events that result in hospitalization, and thus will still be able to observe our primary outcome. In addition, some subjects may receive a heart transplant during the course of the study. Because the disease trajectory and treatment paradigm change significantly with that event, we will censor patients at the time of transplant; the admission to conduct the transplant will count as an event, but follow-up will cease then and patients will be removed from the risk set. We will compare dropout rates by arm, will attempt to find the reasons for missing data and will compare baseline characteristics in participants with complete vs. incomplete follow-up. In secondary analyses we will investigate the sensitivity to modeling assumptions using imputation models and inverse-probability-weighted estimating equations and models that adjust for informative missing data.

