#### 1644 **Summary of statistical analysis plan changes**

1645 There were three amendments to the Data Analysis plan, motivated by an evolving understanding of  
1646 disease management pathways for heart failure patients that impacted how to accurately measure the  
1647 intervention’s effectiveness. The first amendment to the Data Analysis plan in November of 2016 was  
1648 motivated by the addition of censoring criteria for enrolled patients who received an LVAD or transplant  
1649 during study period because the disease trajectory and treatment paradigm change significantly with  
1650 these events. It was determined these patients should be censored at the time of LVAD or transplant.  
1651 The decision to include censoring criteria led to increasing the sample size from 500 to 566 when it was  
1652 determined the censoring rate was higher than expected. The second amendment to the Analysis plan  
1653 in April 2017 clarifies that the Anderson-Gill formulation of the Cox proportional hazards model will be  
1654 used to account not just for time to first admission, but also repeated events within individuals to  
1655 accurately measure the impact of all admissions at the individual level over the course of the  
1656 intervention. The third amendment was in April 2020 and added a secondary endpoint of cause-specific  
1657 rehospitalization, the rationale being that evaluating cause-specific hospital admission will allow a more  
1658 complete understanding of the potential effects of the intervention, by indicating how many of the  
1659 readmissions are due to what cause (e.g., heart failure, MI, stroke, other cardiovascular cause, non-  
1660 cardiovascular cause, etc).

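### Protocol and SAP conflict on censoring at ventricular assist device (VAD) implant, and the protocol's VAD sentence names the intervention arm only

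*Supplement*

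**What the plan says.** Final Protocol section 10 (Analysis Plan) holds two censoring sentences.

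- The first names no arm and concerns transplant only. The plan is to "censor patients at the time of transplant; the admission to conduct the transplant will count as an event", after which the patient leaves the risk set.
- The second adds VAD and names one arm. It begins "If enrolled intervention patients receive a heart transplant or ventricular assist device during their 12 month participation", says that such patients can no longer take part in remote monitoring, and ends "their data will be censored from the date they receive the transplant or VAD going forward".

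The Final SAP (Data analysis plans) has only the transplant rule: "we will censor patients at the time of transplant". It does not mention VAD. Its primary analysis is an "unadjusted intent-to-treat hypothesis test using the Andersen-Gill formulation" of the Cox model, so repeated readmissions all count.

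The Summary of statistical analysis plan changes says the first amendment was "motivated by the addition of censoring criteria for enrolled patients who received an LVAD or transplant", and adds: "It was determined these patients should be censored at the time of LVAD or transplant". It names no arm.

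On entry, section 7.6 excludes patients who are "listed for or being evaluated for a ventricular assist device".

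**The concern.** An intent-to-treat comparison of repeated events needs at-risk time to be defined in the same way in both arms. The only current sentence that ends follow-up at VAD names one arm. Taken at its word for the primary outcome, an intervention patient leaves the risk set at implant, while a usual-care patient stays in it to month 12 and keeps adding readmissions. If VAD patients are readmitted more often after implant, or were at higher risk all along, usual care gathers events that the intervention arm cannot.

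Apart from bias, the primary at-risk set is not uniquely defined. An analyst following the protocol and one following the SAP would build different risk sets from the same data. The DSMB section describes the study as open-label, so the choice should not be left until outcomes are known.

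Detection may differ too. Section 7.2 says control patients are not contacted again after enrollment, whereas intervention patients are in regular contact with staff. VAD dates learned through contact would come mostly from one arm.

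**Working it through.** **Texts side by side**

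| Source | Transplant | VAD | Does the VAD admission count? |
|---|---|---|---|
| Final Protocol, section 10 | both arms | intervention arm only | not stated |
| Final SAP | both arms | neither arm | not stated |
| Summary of changes (evidence of intent only) | no arm restriction | no arm restriction | not stated |

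The asymmetry therefore concerns VAD alone.

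**Inputs from the documents.** 283 patients per arm; 12 months per participant (section 7.3); usual-care 1-year event rate 47%; planned hazard ratio 0.73. The planned ratio reproduces: ln(1 − 0.37)/ln(1 − 0.47) = 0.728. No figure in the plan bears on VAD directly.

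**Assumed, because the documents do not give them.** v = share receiving a VAD (2%, 5%, 10%); k = readmission rate after implant divided by the rate before (0.5 to 3); implant times uniform over the year.

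**Formula under no true effect, intervention arm alone censored at VAD.** VAD patients spend on average half the year after implant. With the pre-implant rate set to 1, the intervention arm shows 1 and usual care shows (1 − v/2) + (v/2)k. The apparent ratio is

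HR = 1/[(1 − v/2) + (v/2)k].

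Example: v = 10%, k = 3 gives 1/(0.95 + 0.15) = 1/1.10 = 0.909.

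**Simulation.** Constant rates (usual care −ln 0.53 = 0.635 per year), gamma frailty with variance 0.5, robust-variance rate ratio (which matches Andersen-Gill under constant rates), 3,000 replicates.

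| v | k | HR, formula | HR, simulated | Rejection at two-sided 0.05 |
|---|---|---|---|---|
| 2% | 0.5 | 1.005 | 1.005 | 4.7% |
| 2% | 2 | 0.990 | 0.988 | 4.6% |
| 2% | 3 | 0.980 | 0.977 | 5.7% |
| 5% | 0.5 | 1.013 | 1.016 | 5.5% |
| 5% | 2 | 0.976 | 0.974 | 5.5% |
| 5% | 3 | 0.952 | 0.955 | 6.3% |
| 10% | 0.5 | 1.026 | 1.029 | 6.2% |
| 10% | 2 | 0.952 | 0.951 | 6.9% |
| 10% | 3 | 0.909 | 0.913 | 11.4% |

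At k = 1 the ratio is 1.00 for every v.

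**If VAD patients also have twice the readmission rate before implant.** With k = 2 the simulated ratio is 0.974 at v = 2% (rejection 5.4%), 0.931 at 5% (9.3%) and 0.874 at 10% (19.2%). Even with k = 1 it is 0.958 at v = 10%, because censoring takes high-risk time out of one arm only.

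**The same rule in both arms.** Censoring both arms or neither gave ratios from 0.995 to 1.006 and rejection from 4.3% to 6.3% (1,500 replicates each). One-sided rejection rates up to about 6% in the table are therefore not clearly above noise.

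**Scale.** At v = 10%, k = 3 the spurious effect is ln(0.909)/ln(0.73) = 0.0954/0.3147, or 30% of the planned log hazard ratio. At v = 5%, k = 2 it is ln(0.976)/ln(0.73) = 0.0243/0.3147, or 8%.

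**The case against.** The best defence is that the second protocol sentence is not a rule for the primary endpoint. Its first consequence, leaving remote monitoring, can apply only to the intervention arm, which would explain the wording. It also repeats transplant, already settled for everyone, and the data it mentions could be device and adherence data. This reading is possible but the weaker one. The sentence stands in the Analysis Plan among the follow-up and censoring provisions and uses the survival term, while adherence data have their own later sentence in different terms. If device data are meant, the text should say so.

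Second, two of the three texts on VAD are arm-neutral. A reader might infer that the trial will in fact drop post-VAD readmissions from one arm. The documents do not support that: the SAP censors neither arm at VAD, and the summary of changes suggests that both arms were intended. The one-arm loss follows only from literal use of the protocol sentence. This objection stands in full against any unconditional claim of bias.

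Third, a reader might take 1 − 500/566 = 11.7% as the VAD rate. The summary ties the larger sample to LVAD and transplant together and states no rate, so the figure cannot be placed on VAD. Because section 7.6 excludes VAD candidates, implants during the study may be few.

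Fourth, an implant admission would ordinarily count as an all-cause readmission, since it starts before the implant. Yet the plan thought it necessary to say this for transplant, and silence on VAD leaves room for two codings.

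**Conclusion.** The conflict is established by the text: the protocol censors at VAD in the intervention arm only, the SAP does not censor at VAD, and neither says how the implant admission is counted. Transplant is handled alike in both arms in both documents. Followed literally for the primary outcome, the protocol sentence gives arm-dependent at-risk time and breaks the intent-to-treat comparison.

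The size and direction of any bias are not established. With assumed VAD shares of 2% to 10% and post/pre rate ratios of 0.5 to 3, the null hazard ratio runs from about 0.91 to 1.03. It falls to about 0.87 if 10% receive a VAD, the rate doubles after implant, and those patients also had twice the rate before it. With few implants it is probably close to 1.

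A reader might also infer that the error favours the intervention. That needs readmissions to rise after implant, or VAD patients to be at higher risk beforehand. The documents state neither, and a falling rate after implant (with no such higher prior risk) reverses the sign.

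**What to change.** - State one analysis rule for VAD, in the same words in Final Protocol section 10 and the Final SAP, that applies identically to both arms.
- Say whether the implant admission counts as an event, as is already done for transplant.
- Take VAD dates in both arms from the same sources: the health system's EMR and the Pennsylvania, New Jersey and Delaware discharge data.
- Add a supportive intent-to-treat analysis that keeps all readmissions to 12 months whatever the VAD or transplant status.
- If the second protocol sentence is meant only for monitoring participation and device data, say so and remove the reference to censoring from it.

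When remote monitoring stops is not at issue. The cost is wording in two documents and one further model run; the records that would hold VAD dates for usual-care patients are already planned for the primary outcome.

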### **6. Secondary Outcome Variable(s)**

In secondary analyses the comparison will also be times to events compared between the intervention and the usual care arm for cause-specific rehospitalizations. Cost-effectiveness ratios will be calculated as the difference in costs divided by the difference in rehospitalization rate calculated under Specific Aim 3 for the “within-trial” analysis.

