### **7. Study Design**

#### *7.1. Phase*

Phase III

*7.2. Design*

Participants in this study will be identified using Penn Data science through regular feeds sent to the research coordinators. Potentially eligible patients will be identified while they are discharged from a UPHS hospital and provided information on the study, which will either be delivered by study staff or channeled through the health care provider. Participants will be recruited after discharge by phone call in the few days post-discharge. During enrollment, the coordinator will read the IRB-approved consent/HIPAA script and the participant will be asked to provide verbal consent and verbal HIPAA authorization for use of their data in the study. Once a patient provides verbal consent, the coordinator will select this option on the consent/HIPAA form on the patient profile created during the enrollment call on the WTH platform. After the patient has consented to study participation and study eligibility has been confirmed, the coordinator will enter basic demographic information for the patient onto the WTH platform and will collect information on the UPHS managing physician that the patient will be following up with for CHF. Participants will also be asked for their SSN to complete a W-9 form on the patient profile on the WTH platform. Participants will then be randomized to either the intervention or usual care (283 intervention, 283 control). Control patients will be thanked for their participation, compensated \$25 for enrolling and will not be contacted again. Intervention participants will (1) be given a medication adherence device for their diuretic and a scale; (2) asked to provide the coordinator with name and contact information of a family member or friend to serve as a support partner; (3) will be assigned a 2-digit number to be used as part of the lottery-based engagement incentives in which eligibility to win will be conditional on medication adherence and registering a weight measurement; and (4) will determine their preferences for WTH platform communication methods during the study. In regards to support partners, the coordinator will reach out to the family member or friend, whose contact information will be provided by the patient during the enrollment process, to ask them to serve as the patients support partner. He or she will be given the option of receiving a text message, an e-mail, or interactive voice recording (IVR) from the WTH platform. The coordinator will place the call to the potential support partner after the patient is enrolled. Participants will be sent the medication adherence device and scale and the coordinator will provide the participant with a brief tutorial on how the devices should be used, and will be available for follow up phone call to ensure proper set up of devices in the home. Participants will be told that they should receive the medication adherence device and scale in the next few days to the mailing address confirmed during the enrollment process. On the enrollment call, the coordinator and patient will also schedule an appointment to setup their devices. Following enrollment, we will add a note to the patients electronic medical chart saying that they are an active participant in this study. We will also contact the patients managing physician through PennChart and by email to inform them of their patients enrollment in the study. During the device setup process, the coordinator will then explain to the patient that he or she will receive daily feedback on adherence to their medication and registering a weight measurement. This feedback will include information on the lottery; patients will be eligible for the daily lottery if they had adhered to their medication and if they had registered a weight measurement on the previous day. Patients will be asked whether they would like to receive the daily feedback via text message, e-mail or IVR. If a patient is non-adherent to medication and registering a weight measurement for 2 days, an automated call will be made to the patient to stress the importance of taking medication and weighing in and an automated feedback message will be sent to the patients support partner. On 3rd day of non-adherence, study staff will call the patient. On 4th day of non-adherence, study staff will call the support partner. Finally, on 5th day of non-adherence, study staff will send a note to the patients managing clinician through PennChart. All participants will be instructed to call study staff for any questions or problems related to device use.

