#### 1629 Cost effectiveness analysis

1630 To assess the cost-effectiveness of the interventions, we will use analytic methods for economic  
1631 evaluations in clinical trials. Our approach will be similar to Specific Aim 3 using cost as the outcome. We  
1632 will use generalized linear models to adjust for the stratification variable and other factors. Cost-  
1633 effectiveness ratios will be calculated as the difference in costs divided by the difference in  
1634 rehospitalization rate calculated under Specific Aim 3 for the “within-trial” analysis, with parametric 95%  
1635 CIs for the cost per percentage point increase in adherence and acceptability curves. Standard errors  
1636 and the correlation of the difference in cost and effect will be obtained using a bootstrap procedure. A  
1637 further cost-effectiveness analysis from the “societal perspective” will be conducted to assess the  
1638 impact of the rehospitalization rate reductions measured as cost per QALY gained. To address  
1639 uncertainty in the micro simulation model, we will also conduct a probabilistic sensitivity analysis  
1640 (PSA) by defining probability distributions for the variables in the model used to calculate costs and  
1641 effectiveness. We will use the results of the PSA to calculate confidence (or credible) intervals and  
1642 acceptability curves.

1643

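### The 95% interval for the within-trial cost-effectiveness ratio is specified per point of adherence, which is not the ratio's denominator and is not recorded in usual care

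*Supplement*

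**What the plan says.** Cost-effectiveness relative to usual care is the first of the two secondary aims in Final Protocol section 4.2. Section 6 gives the ratio: "ratios will be calculated as the difference in costs divided by the difference in rehospitalization rate calculated under Specific Aim 3". Section 10 and the Final SAP (Cost effectiveness analysis) repeat that definition and then attach the interval to something else: "parametric 95% CIs for the cost per percentage point increase in adherence and acceptability curves" in the protocol, with the same phrase in the SAP, "CIs for the cost per percentage point increase in adherence and acceptability curves".

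Both documents add that standard errors and "the correlation of the difference in cost and effect will be obtained using a bootstrap procedure". They also plan a separate societal analysis of the "rehospitalization rate reductions measured as cost per QALY gained", with a probabilistic sensitivity analysis.

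On data collection, sections 7.2 and 9.2 give the wireless pill device and the scale to intervention participants only. Section 7.2 says that control patients, once enrolled and paid, "will not be contacted again".

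**The concern.** A confidence interval should belong to the estimate it accompanies. Here the estimate has rehospitalization in the denominator and the interval has adherence. The second quantity also needs an adherence value in each arm, and the plan describes no source for one in usual care.

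The effect is defined by pointing to Specific Aim 3. Section 4 of the Final Protocol lists one primary and two secondary aims and no Specific Aim 3, so the pointer leads nowhere.

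At stake is the uncertainty statement for the first-listed secondary aim. An analyst following the text would have to depart from it, and would have to choose the effect measure, possibly after seeing the data.

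**Working it through.** The plan states no figure for this interval, so there is nothing to reproduce. The check sets definitions against data.

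**1. Ratio and interval**

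| Quantity | Numerator | Denominator | Source |
|---|---|---|---|
| Ratio to be estimated | difference in cost | difference in rehospitalization rate | Protocol 6 and 10; SAP |
| Quantity given the 95% interval | cost | percentage-point increase in adherence | Protocol 10; SAP |
| Societal analysis | cost | QALYs gained | Protocol 10; SAP |

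The first two rows stand in one sentence and have different denominators.

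**2. What each arm supplies**

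| Data | Intervention (about 283) | Usual care (about 283) |
|---|---|---|
| Adherence by device and scale | yes | no device, no scale |
| Adherence by refill, claims or self-report | none described | none described |
| Readmissions | Penn Medicine records and PA, NJ and DE discharge data | same |

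The between-arm adherence difference is adherence(intervention) − adherence(usual care). Its second term has no data source, so the difference cannot be formed. The rehospitalization difference needs no patient contact and is available in both arms.

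Section 11 does say that the device supplies adherence data from each participant. That can only mean each participant who holds one. The rule in section 10 that removes days in hospital, rehab or a SNF from adherence adds no control-arm source.

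**3. The pointer to Specific Aim 3**

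It appears once in section 6, and twice each in section 10 and the Final SAP. Counting the listed aims in order does not rescue it: the third is cause-specific rehospitalization, whereas the primary outcome is readmission for any cause.

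**4. Whether the missing definition matters**

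Rate could mean the proportion readmitted, as in the planned 47% against about 37%, or mean readmissions per patient. As an illustration, take those planned proportions.

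- Proportion: 0.47 − 0.37 = 0.10 per patient.
- Mean readmissions, if nobody is readmitted twice: also 0.10.
- Mean readmissions, assuming a constant rate with independent repeats and no deaths: −ln(0.53) = 0.635 and −ln(0.63) = 0.462, a difference of 0.173.

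For the same cost difference, the two ratios differ by a factor between 0.10/0.10 = 1.0 and 0.173/0.10 = 1.7 under these two assumptions. The documents give no repeat-admission rate, so this shows only that the choice is not cosmetic.

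**The case against.** The strongest reply is that this is one mislabelled phrase. The ratio is stated explicitly, its inputs are observed in both arms, and the bootstrap of cost and effect differences supplies what an interval and an acceptability curve require. All of that stands, and it limits the point.

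A reader might infer that the cost-effectiveness analysis as a whole cannot be done. The documents do not support that. Only the interval on adherence is out of reach; the cost-per-QALY analysis does not use adherence either.

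A reader might also argue that the primary Andersen-Gill model gives a hazard ratio and so leaves no rate difference to divide by. But the cost-effectiveness text does not take its denominator from that model. It names a rate difference, which can be computed directly from the arms.

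Third, a reader might object that a parametric interval for a ratio misbehaves when the effect is near zero, and size the fault by power. For 47% against 37% with 283 per arm, the standard error is √[(0.47×0.53 + 0.37×0.63)/283] = 0.041, so z = 0.10/0.041 ≈ 2.42 and power is about 68%. The interval for the difference would then include zero in roughly one trial in three. This is a property of a first-event comparison. It does not measure the mislabelling, would remain after the wording is corrected, and does not carry over to a count of repeat admissions. Bootstrap standard errors, their correlation and acceptability curves already address much of the instability.

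**Conclusion.** The point holds in a limited form. In the current protocol and SAP, the 95% interval for the within-trial ratio is specified for a different quantity, and that quantity cannot be estimated against usual care because adherence is unrecorded for every control. The effect measure that should replace it is not defined, since the aim it cites is absent from the Final Protocol.

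This rests on the documents describing no adherence source for controls; if one exists elsewhere, the interval could be computed but would still not belong to the stated ratio. The reach is one interval and one definition within a secondary aim. The primary analysis, the ratio, the acceptability curves and the cost-per-QALY analysis are not affected by the adherence wording. It should be corrected before the economic analysis is run.

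**What to change.** In Final Protocol section 10 and the Final SAP, replace the adherence denominator of the interval with cost per unit reduction in 12-month all-cause rehospitalization.

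In sections 6 and 10 and the SAP, replace the references to Specific Aim 3 with an explicit effect measure. Either the between-arm difference in the proportion readmitted, or the difference in mean readmissions per patient, over 12 months would serve; name one, with costs over the same period. The text should also say how that common period applies to patients censored at transplant or VAD.

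State that the interval and the acceptability curve both come from the planned bootstrap of the cost and effect differences. Reporting incremental net benefit is optional. If a ratio on adherence is really wanted as well, name a control-arm source for it.

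The cost is an edit to both documents. No new data are needed for the rehospitalization ratio, and the bootstrap is already in the plan.
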